### Justification of the length of follow-up

The occurrence of SSIs happens primarily in the first three months post-operatively. The Centers for Disease Control (CDC) defines the timing of SSI as within the first 30 days unless a foreign body is implanted. In the presence of an implanted foreign body the surveillance period is extended to one year. Since the majority of orthopaedic surgeries result in the implantation of a metallic body we have extended the follow-up period to one year. Given the fact that the primary outcome measure is a composite measure related to the healing of a wound we will analyze the data after all participants have completed six-week follow-up. A phone survey will be performed at one year in order to conform with the CDC definition of SSI.

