### Research question

In adult patients undergoing orthopaedic procedures does the wound closure material (sutures versus metallic staples) influence the occurrence of post-operative wound complications within the first year?

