### Primary outcome measure

The primary outcome measure will be a composite outcome encompassing all causes of wound complication. The clinical relevance of the primary outcome measure stems from the fact that the components of the composite outcome all represent occurrences that are patient important. The components consist of the following events:

1. Surgical site infection as defined by:

• Use of intravenous antibiotics

• Use of oral antibiotics

• Re-operation at same site

2. Wound drainage occurring after post-operative day two requiring a dressing change.

3. Wound Necrosis defined as blackening of the skin edges at the incision site or skin slough observed by providers or the participant.

4. Suture Abscess defined as the expulsion of deep suture material and purulent material without surrounding erythema.

5. Peri-incision Blistering defined as blistering at the edge of the incision along the entire length. Blistering at dressing tape site will be excluded from this definition, however, blistering due to wound tape application which is contiguous with the wound edge will be considered an event.

6. Wound Dehiscence as defined by the loss of apposition of the skin edges visible to the eye along the length of the incision.

7. Material Sensitivity as defined by a local reaction to metal or suture material resulting in skin changes along the entire incision length.

The primary outcome measure will be assessed during admission by review of the patient chart by site coordinators who will be blinded to the treatment allocation. Outcome assessors will be uniformly trained in the definitions of the components of the composite outcome score. Outpatient complications will be recorded through self-report questionnaires administered by site coordinators. All deceased patients will also be reviewed for occurrence wound complications. Final determination of events will be made by an independent outcomes adjudication committee based on blinded clinical data identified by the committee as necessary for the determination of complications. A sample of non-infected participants will also be reviewed by the committee as a negative control.

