### Interim analysis

Interim analysis will be performed by a Data Safety and Monitoring Committee blinded to the treatment groups. Analyses will take place at the half-way point of patient recruitment. The alpha spending function approach to setting significance levels will be used. The trial will be stopped if a difference is found in the complication rates using a significance level of 0.15% based on the O’Brien-Flemming boundaries for a group sequential trial.

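### The question concerns the first year, the only stated final analysis comes at six weeks, and the primary composite has no time window

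*Protocol article*

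**What the plan says.** - **Research question:** the trial asks whether closure material will "influence the occurrence of post-operative wound complications within the first year".
- **Justification of the length of follow-up:** because most of the operations leave a metallic implant, "we have extended the follow-up period to one year". The section then says "we will analyze the data after all participants have completed six-week follow-up", on the ground that "the primary outcome measure is a composite measure related to the healing of a wound". It adds: "A phone survey will be performed at one year in order to conform with the CDC definition of SSI". It also says: "The occurrence of SSIs happens primarily in the first three months post-operatively".
- **Primary outcome measure:** "The primary outcome measure will be a composite outcome encompassing all causes of wound complication". Seven components follow, SSI first. Neither the composite nor any component is given a closing date.
- **Secondary outcome measures:** SSI at one year is not among them.
- **Data analysis:** binary outcomes are compared with Fisher's exact test (the Abstract says chi-squared). The section does not mention the one-year data.
- **Interim analysis:** "Analyses will take place at the half-way point of patient recruitment". This is the only other analysis point, and it falls before the final one.

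**The concern.** The time window is part of what a binary primary outcome measures. Here the question carries one window, the analysis is timed by another, and the outcome definition has none. Both time points are given a reason, but the article does not say which of them defines the primary result.

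Two things are at stake. First, a six-week result could be reported as the answer to a one-year question. Second, while the window stays open it can be settled after results are known. The infections that motivate one-year follow-up, those around an implant, are the events whose place in the primary result is unclear.

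**Working it through.** The plan gives no figure on this point to reproduce. The check is whether any reading of the six-week sentence makes the sections agree, with simple arithmetic for the second reading.

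**Reading A: six weeks is the outcome window.**
- Events from week 6 to week 52 are not counted, so the primary result is a six-week risk and the research question is about a different quantity.
- The article places most SSIs in the first three months, about 13 weeks. A six-week window closes before half of that period has passed.
- The one-year survey then feeds neither the primary outcome nor any listed secondary outcome.

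**Reading B: six weeks is only the data cut, and all events known by then count.**
- Inputs: accrual A = 24 months = 104 weeks (Anticipated recruitment rate); analysis at L = 6 weeks after the last enrolment (Justification of the length of follow-up). Uniform accrual is an assumption, and loss to follow-up is ignored.
- Participants who have reached one year are those enrolled in the first A + L − 52 = 104 + 6 − 52 = 58 weeks.
- Share at one year = 58/104 = 56%; share short of one year = 46/104 = 44%.
- Mean follow-up, capped at 52 weeks: those short of one year range from 6 to 52 weeks, mean 29. So (46 × 29 + 58 × 52)/104 = 4350/104 = 41.8, about 42 weeks.
- Sensitivity to accrual shape: with linearly rising accrual the share at one year is (58/104)² = 31%; with linearly falling accrual it is 1 − (46/104)² = 80%.
- Fisher's exact test, like chi-squared, compares crude proportions. On such data the proportion is an average over follow-up from 6 to 52 weeks. It is neither the six-week nor the one-year risk, and it depends on how fast the sites happened to recruit.

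**Waiting for a complete one-year outcome.** The analysis would move from 6 to 52 weeks after the last enrolment: 52 − 6 = 46 weeks later.

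**Why the pilot window matters (conditional).** The sample size uses a pilot complication rate whose value and window are not in the readable text; the details are in a figure that is not shown. With a 25% relative reduction, two-sided alpha 0.05 and 80% power,

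n per arm = [1.960·√(2p̄(1−p̄)) + 0.842·√(p₁(1−p₁) + p₂(1−p₂))]² / (p₁−p₂)²,

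where p̄ is the mean of p₁ and p₂. Assumed control rates p₁ of 5%, 10%, 20% and 30% give about 4,202, 2,005, 906 and 540 per arm. These are illustrations, not the trial's figures. They show only that the required number depends strongly on the rate, and so on the window over which it is counted.

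**The case against.** The strongest reply is that the follow-up section already explains both time points. Six weeks suits a wound-healing composite, since drainage, necrosis, blistering and dehiscence are events of the healing incision. One year serves the surveillance definition of SSI where there is an implant. On this reading the design is a six-week composite plus one-year SSI surveillance, and the research question is loosely worded. This is a sensible design and may well be what was intended. But the article does not say so: the question names the first year, the composite has no window, and one-year SSI is not listed as an outcome. A fuller protocol or SAP may add detail, but it would have to choose between statements that conflict here.

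It also stands that the three-month sentence concerns SSI, one of seven components, so it does not show that six weeks misses much of the composite. Both arms share the same calendar, so no bias between the arms is shown.

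Four stronger inferences are tempting and not supported:
- *That late implant infections cannot enter the primary result.* This follows under Reading A only. Under Reading B they enter for some participants.
- *That the trial cannot answer its one-year question.* One-year SSI data are to be collected. What is missing is a stated role for them, and the survey is tied to SSI, not to the whole composite.
- *That the alpha plan is breached by a second test at one year.* No second test of the composite is planned. The 4.7% level allows for the interim look, so the issue would arise only if such a test were added.
- *That the trial loses power.* This would follow only if the pilot rate were a one-year rate, which the readable text does not say. If it was a six-week rate, a six-week analysis loses nothing.

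**Conclusion.** The point holds as a contradiction in the stated text. The research question and the follow-up period say one year, the only stated final analysis is timed at six weeks, and nothing fixes the window of the primary composite. Neither reading of the six-week sentence reconciles the sections. The first gives a six-week answer to a one-year question. The second gives a crude proportion over mixed follow-up, with about 56% of participants at one year under uniform 24-month accrual (31% to 80% across the accrual shapes tried).

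The contradiction needs no assumption; only these percentages rest on assumed accrual. No loss of power, inflation of alpha or bias between arms is claimed. The window should be settled before any comparison by arm is seen, because it defines what the trial estimates.

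**What to change.** State one fixed window for the primary composite, in the same terms, in the research question, the primary outcome definition and the follow-up section. Two choices are coherent:

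1. **Six weeks.** The primary outcome is the adjudicated composite by six weeks for every participant, with later events not counted however early the participant enrolled. Reword the research question to match. Name adjudicated SSI by one year as a secondary outcome, reported with a confidence interval and not as a second test of the primary hypothesis.
2. **One year.** Keep the question as it is, define the composite by one year, and hold the primary analysis until the one-year survey is complete for all participants. Because the survey is described only in relation to SSI, also state that it covers the other components.

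The first fits the existing timetable. In either case, confirm that the pilot rate behind the sample size was counted over the chosen window, and recalculate if it was not.

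The first choice costs wording only, with no extra participants or visits, and narrows the headline claim to six weeks. The second delays the main report by about 46 weeks.

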### Sample size determination

Estimates of sample size necessary to definitively test the hypothesis in this study were calculated using rates of wound complications found in a pilot study which included 148 participants. A relative risk reduction of 25% in wound complications was chosen as a minimal clinically important difference in wound complications. Sample sizes are presented graphically for varying powers and with a constant α level of 0.05 (Figure 
2). Microsoft Excel (Redmond, WA) was utilized to perform calculations. The details of the sample size calculation are presented in Figure 
2.

**Figure 2 F2:**
[figure not shown]
Projected sample size based on a relative risk reduction of 25% for wound complications and using an alpha of 0.05.

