### Data analysis

All anatomic sites will be analyzed together and separately using Stata (College Station, TX). Dichotomous primary and secondary outcome measures will be analyzed using Fisher’s exact test. Stratification based on potential confounding variables will be performed. A multivariable analysis employing logistic regression will be performed to assess the possible impact of empirical confounding by putative risk factors of the binary outcomes. Length of stay, visual analogue scale pain measurements and patient satisfaction data will be compared using a two-way ANOVA. Linear regression will be performed on continuous variables to assess the possible impact of empirical confounding by putative risk factors. A 4.7% level of significance will be considered significant based on the adjustment of significance level for the interim analysis.

Subgroup analyses will be performed comparing the use of sutures and staples in trauma versus elective procedures and primary versus revision procedures as appropriate.

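### The 4.7% final significance level is stricter than the 0.15% interim level requires, so the final test has slightly less power than a sample-size curve drawn at alpha 0.05

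*Protocol article*

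**What the plan says.** Three sections of the Protocol article bear on the significance level.

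- **Sample size determination and the Figure 2 caption.** The text says "Sample sizes are presented graphically for varying powers and with a constant α level of 0.05", and the caption repeats it, giving a size based on a "relative risk reduction of 25% for wound complications and using an alpha of 0.05". The target effect is fixed in the same section: "A relative risk reduction of 25% in wound complications was chosen as a minimal clinically important difference in wound complications". The readable text gives no sample size, control rate or single power target. These are left to Figure 2, which is not shown.
- **Interim analysis.** There is one look: "Analyses will take place at the half-way point of patient recruitment". The stopping rule reads "The trial will be stopped if a difference is found in the complication rates using a significance level of 0.15" (the figure is a percentage). The section names the alpha spending approach and O'Brien-Fleming boundaries. It does not say whether 0.15% is two-sided or per side.
- **Data analysis.** "A 4.7% level of significance will be considered significant based on the adjustment of significance level for the interim analysis". This section names Fisher's exact test for dichotomous outcomes, while the Abstract names the chi-squared statistic.

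**The concern.** The level used to size the trial (0.05) and the level used to judge the final result (4.7%) differ, and the text does not connect them. A test at 4.7% rejects less often than the same test at 5%. Power read from a curve drawn at 0.05 is therefore a little higher than the power of the final test, whatever the control rate.

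A gap of this kind is expected when an interim look has spent some alpha. The question is whether 4.7% is the right remainder after a 0.15% look at half recruitment. If it is stricter than necessary, the trial gives up a little power for no gain in error control. A final p-value between 4.7% and about 4.9% would also be called non-significant although the overall 5% allows it. That decision threshold should be settled before the data are seen.

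**Working it through.** **Inputs from the Protocol article.** Sizing alpha 0.05; final level 0.047; interim level 0.0015; one look at half recruitment, taken as information fraction 0.5; relative reduction 25%; equal allocation.

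**Assumptions.** Tests are two-sided, because the alternative hypothesis is that the rates differ. The control rate is not in the readable text, so 5% to 40% was tried. There is no visible size or power in the plan to reproduce.

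**1. Overall alpha of the stated pair.** With one look at information fraction 0.5, the interim and final z-statistics are bivariate normal with correlation √0.5 = 0.707. The overall two-sided error is 1 − P(|Z₁| < c₁ and |Z₂| < c₂) under no difference. The final critical value for 0.047 is 1.986. The interim critical value is 3.175 for 0.15% two-sided and 2.968 for 0.15% per side (0.30% two-sided).

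| Reading of 0.15% | Overall alpha with final 4.7% | Final level that gives overall 5% |
|---|---|---|
| Two-sided | 4.74% | 4.96% |
| Per side | 4.80% | 4.90% |

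The per-side reading has some support. An O'Brien-Fleming-type spending function with 2.5% per side spends 0.305% two-sided at half information, which is about 0.15% per side. The classic two-look O'Brien-Fleming pair is 0.52% and 4.80%. Neither form gives 4.7%.

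**2. Power of the final test when the size was set at 0.05.** For a size that gives power P at alpha 0.05, the expected z-statistic is θ = z(0.975) + z(P). Power at 0.047 is Φ(θ − 1.9863). The control rate drops out.

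- Nominal 80%: θ = 1.9600 + 0.8416 = 2.8016; Φ(2.8016 − 1.9863) = Φ(0.8153) = 79.3%.
- Nominal 90%: θ = 1.9600 + 1.2816 = 3.2415; Φ(3.2415 − 1.9863) = Φ(1.2552) = 89.5%.

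A rate-by-rate check with the pooled-variance formula gave the same answer to within 0.1 point for control rates of 5% to 40%. For example, with a control rate of 20% and 906 per arm, power is 80.0% at 0.05 and 79.3% at 0.047. The largest loss over nominal powers of 50% to 95% is about 1 point, at 50%.

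**3. Counting rejections at the interim look.** The chance of rejecting at either look with the 0.15%/4.7% pair is 79.3% (79.4% per side) at nominal 80%, and 89.6% at nominal 90%. A stopping level this strict adds almost nothing back.

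**4. Power with the consistent final level.** With 0.15% two-sided and 4.96%, overall power at nominal 80% is 79.95%. With 0.15% per side and 4.90%, it is 79.85%. The loss falls to about 0.1 point.

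**5. Fisher's exact test.** Suppose the curve came from the pooled normal formula without continuity correction. Exact enumeration of Fisher power at 0.047, at the sizes that formula gives for 80% power, is then 77.8%, 77.6% and 77.4% for control rates of 10%, 20% and 30%. About 1.5 points of that loss come from the choice of test and would be there at alpha 0.05 too. If the curve used a continuity correction, most of that part disappears. The formula cannot be seen.

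**The case against.** The strongest reply is that nothing here is contradictory. The Data analysis section says the 4.7% is an adjustment for the interim look. In a two-look design 0.05 is naturally the overall level, with 0.15% and 4.7% as the nominal levels at each look. The pair keeps the overall error below 5%, the power effect is under one point at 80% or 90%, and a control rate taken from 148 pilot patients is far less certain than that. All of this stands. It means that sizing at 0.05 is not wrong and that the point is minor.

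It can be added that, if 0.15% is per side, 5% − 2 × 0.15% = 4.7% exactly. That may be where the figure comes from, although the document does not say so. Plain subtraction gives a valid but conservative threshold, because it ignores the correlation between the two looks. The spending approach named under Interim analysis takes that correlation into account and leads to 4.90% on the same reading. The reply therefore explains 4.7% without making it the value that the stated method produces.

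Two stronger readings are tempting. A reader might infer that every power in Figure 2 is too high. The figure is not shown, and it cannot be known whether its sizes were rounded up or already allow for the interim look. A reader might also infer a loss of more than 2 points once Fisher's exact test is counted. That rests on an assumed sizing formula, and the Abstract names a different test for the same outcomes.

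**Conclusion.** The point holds in a limited form. The 0.05 used for sizing is acceptable as an overall level. The final level of 4.7% does not follow, by the named alpha spending approach, from an interim level of 0.15% at half recruitment: the pair spends 4.74% (4.80% if per side) instead of 5%. The cost is about 0.7 point of power at nominal 80% and about 0.5 point at 90%, relative to a curve at 0.05. Type I error is not inflated.

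These figures assume two-sided testing, an interim look at half the information, and a curve without allowance for the look. They do not depend on the control rate. The documents do not support a claim about particular sizes or powers in Figure 2, nor a firm figure for any further loss from the exact test. This is a minor correction to a decision threshold and its wording.

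**What to change.** Preferred: state whether 0.15% is two-sided or per side, set the final significance level to the value that goes with it (4.96% if two-sided, 4.90% if per side), and say in the sample-size section that 0.05 is the overall two-sided level of the two-look design.

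Alternative: keep 4.7% as a deliberately conservative threshold, say so, and restate the power in Figure 2 at that level.

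The cost is one recalculation and a few words of text. If 4.7% is kept, the stated power becomes slightly lower. Neither route needs extra patients.

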### Anticipated recruitment rate

In a pilot site it was found that 60% of patients approached consented to participate. A recruitment model was created taking into account expected site fatigue and differences in consenting efficiency between the United States and Canada. Based on the combined clinical volume at the five sites it is expected that the study will be completed with enrolment after 24 months of recruitment. Additional international sites are currently being developed to ensure that this target is met and to improve the generalizability of the results.

### Data analysis

All anatomic sites will be analyzed together and separately using Stata (College Station, TX). Dichotomous primary and secondary outcome measures will be analyzed using Fisher’s exact test. Stratification based on potential confounding variables will be performed. A multivariable analysis employing logistic regression will be performed to assess the possible impact of empirical confounding by putative risk factors of the binary outcomes. Length of stay, visual analogue scale pain measurements and patient satisfaction data will be compared using a two-way ANOVA. Linear regression will be performed on continuous variables to assess the possible impact of empirical confounding by putative risk factors. A 4.7% level of significance will be considered significant based on the adjustment of significance level for the interim analysis.

Subgroup analyses will be performed comparing the use of sutures and staples in trauma versus elective procedures and primary versus revision procedures as appropriate.

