**Methods/Design:**

A parallel group randomized controlled trial with institutional review board approval will be conducted. Patients will be randomized intraoperatively to have skin wounds closed with sutures or staples. Dressings will be used to maintain blinding outcome assessors. The primary outcome measure will be a composite all-cause wound complication outcome measure composed of: infection, wound drainage, wound necrosis, blistering, dehiscence, suture abscess and material sensitivity reaction. An independent review board blinded to treatment assignment will adjudicate suspected complications based on clinical data. All deceased patients will also be reviewed. An interim analysis of complications will take place after half of the patients have been recruited. All data will be analyzed by a blinded statistician. Dichotomous primary and secondary outcome measures will be analyzed using the Chi-squared statistic. Continuous outcome measures will be analyzed using Student's t-test. Subgroup analysis will compare infection rates using sutures versus staples in each anatomic area (upper extremity, pelvis/acetabulum, hip/femur, knee, ankle). A further subgroup analysis will be conducted comparing trauma patients to elective surgery patients. Non-infected revision surgery will also be compared to primary surgery.

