### Trial design

#### Parallel Group Randomized Controlled Trial with Economic Analysis

Recruitment of patients under the care of subspecialists in Orthopaedic Trauma, Spine, Adult Reconstruction and Upper Extremity Reconstruction will take place concurrently with the same trial infrastructure. Patients will be recruited by the office assistant, research assistant or delegate of the treating surgeon administering the surgical consent form. Verbal consent will be obtained for trauma patients unable to sign a consent form. Written consent will be obtained within 24 hours of treatment allocation. Patients eligible but not enrolled will be documented. Participant flow through the study can be seen visually in Figure 
1.

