### Method of allocation to groups

Randomization will be concealed and will be allocated at the time of skin closure. Randomization will be completed using an online randomization program. Block randomization with randomly sized blocks between eight and 12 participants will be employed to ensure an equal number of participants in each group for each subspecialty. Group assignments will be revealed by the online randomization program and the time of the randomization will be recorded electronically. Times of randomization will be compared with operative notes retrospectively to ensure concealment is being maintained.

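### The abstract and the Methods name different primary tests (chi-squared and Fisher's exact), and neither test is stratified by the subspecialty used in randomisation

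*Protocol article*

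**What the plan says.** The protocol article fixes the test for the binary outcomes twice.

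- Abstract, Methods/Design: "Dichotomous primary and secondary outcome measures will be analyzed using the Chi-squared statistic".
- Methods, Data analysis: "Dichotomous primary and secondary outcome measures will be analyzed using Fisher’s exact test".

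It does the same for the continuous outcomes.

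- Abstract, Methods/Design: "Continuous outcome measures will be analyzed using" Student's t-test.
- Methods, Data analysis: "Length of stay, visual analogue scale pain measurements and patient satisfaction data will be compared using a two-way ANOVA". The second factor of that ANOVA is not named.

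Neither place is a log of changes, so both statements are current text.

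On randomisation, the Method of allocation section uses blocks of random size "to ensure an equal number of participants in each group for each subspecialty". The Trial design section names four subspecialties: trauma, spine, adult reconstruction and upper extremity reconstruction. On adjustment, Data analysis adds "Stratification based on potential confounding variables will be performed" and a logistic regression to look for confounding by risk factors. Neither sentence mentions subspecialty, and neither is presented as the primary test. The final significance level is 4.7%.

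**The concern.** A confirmatory trial needs one primary p-value that can be identified before the data are seen. Here two tests are on record for the same outcome. They are not interchangeable, because Fisher's test is more conservative than the uncorrected chi-squared test, so a borderline result could be significant under one and not under the other. A reader of the final report could not tell whether the test had been chosen beforehand.

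The second part concerns efficiency. Balancing the arms within subspecialty removes between-subspecialty variation from the treatment comparison. A test that ignores the strata still counts that variation in its standard error. If complication risk differs between, say, trauma and upper-extremity surgery, the test is then conservative, and some precision gained by the design goes unused.

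**Working it through.** The text gives no event rate, target sample size or power; these are left to Figure 2, which is not shown. There is thus no stated figure to reproduce, and the control rates and stratum rates below are assumptions. From the documents come the 25% relative risk reduction, alpha 0.05 for the sample size, the 4.7% final level, equal arms and four subspecialties. Tests are taken as two-sided because the alternative hypothesis is a difference in either direction.

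**Step 1. Illustrative size.** With p1 = 0.20 and p2 = 0.75 × 0.20 = 0.15, the mean is 0.175 and

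n per arm = [z_a √(2 × 0.175 × 0.825) + z_b √(0.20 × 0.80 + 0.15 × 0.85)]² / 0.05².

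- Alpha 0.05, 80% power: (1.9600 × 0.5373 + 0.8416 × 0.5362)² / 0.0025 = 905.4, so 906.
- Alpha 0.047, 80% power: (1.9863 × 0.5373 + 0.8416 × 0.5362)² / 0.0025 = 922.5, so 923.

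**Step 2. Can the two tests disagree?** For 185/923 against 152/923 there are 337 events and 1,509 non-events. With equal arms, chi-squared = N × (difference in events)² / (events × non-events) = 1846 × 33² / (337 × 1509) = 3.953. The critical value at 4.7% is 1.9863² = 3.945.

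- Chi-squared p = 0.0468: significant.
- Fisher p = 0.0537: not significant.

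A second example is 165/550 against 135/550: chi-squared = 1100 × 30² / (300 × 800) = 4.125, p = 0.0423; Fisher p = 0.0495. Again only chi-squared passes.

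**Step 3. Operating characteristics at 4.7%, by exact binomial enumeration.**

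| Control rate | n per arm | Power, Fisher | Power, chi-squared | Size, Fisher | Size, chi-squared |
|---|---|---|---|---|---|
| 20% | 906 | 77.6% | 79.4% | 4.1% | 4.7% |
| 10% | 2043 | 78.6% | 80.2% | 4.1% | 4.7% |
| 20% | 923 | 78.4% | 80.2% | 4.1% | 4.7% |
| 30% | 550 | 78.2% | 80.2% | 4.0% | 4.7% |
| 40% | 363 | 78.0% | 80.2% | 3.8% | 4.6% |

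Fisher's test gives up about 2 points of power throughout. At 906 per arm and 20% against 15%, the two tests reach different decisions in 79.4 − 77.6, about 1.7% of trials before rounding.

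**Step 4. Effect of ignoring the strata.** Four equal strata, constant risk ratio 0.75, 100,000 simulated trials per case, tests at 4.7%.

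| Stratum control rates | n per arm | Power, stratified (Cochran-Mantel-Haenszel) | Power, unstratified chi-squared | Size, unstratified |
|---|---|---|---|---|
| 20% in all | 923 | 80.1% | 80.1% | 4.6% |
| 10, 15, 25, 30% | 923 | 81.2% | 80.3% | 4.3% |
| 5, 10, 25, 40% | 923 | 84.1% | 81.5% | 3.4% |
| 2, 8, 20, 50% | 923 | 87.4% | 82.4% | 2.5% |
| 15, 25, 35, 45% | 550 | 82.0% | 80.7% | 3.9% |
| 10, 20, 30, 60% | 550 | 85.4% | 81.6% | 2.9% |

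A hand check on the size column: the unstratified test uses variance p(1 − p) at the mean rate, 0.20 × 0.80 = 0.160. The balanced design leaves only the mean within-stratum variance. For 5, 10, 25 and 40% that is (0.0475 + 0.09 + 0.1875 + 0.24) / 4 = 0.1413. The effective critical value becomes 1.9863 × √(0.160 / 0.1413) = 2.114, a two-sided size of 3.5%, against 3.4% simulated.

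**The case against.** The strongest defence has four parts.

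- **An abstract is only a summary.** It may leave the test out, but here it names a different one, and nothing in the article says which governs. The contradiction stands whatever rates are assumed.
- **An unstratified primary test with adjusted supporting analyses is valid.** This is right. Every size in the working is at or below about 4.7%, so nothing is inflated. Stratifying is an efficiency recommendation, not the correction of an invalid method. In the assumed cases with unequal strata the unstratified chi-squared test still has 80% power or more; the stratified test adds to that.
- **The Data analysis section already stratifies and adjusts.** In part. It does not exclude subspecialty, but it does not name it, and it does not make either analysis the primary one. A reader might infer that covariates will be picked after imbalance is seen. The text does not say so, and the covariate list is ordinary content for an analysis plan that is not shown.
- **The two-way ANOVA may already have subspecialty as its second factor.** It may. That would settle the Methods wording for the continuous outcomes, but not the conflict with the abstract's t-test.

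A reader might also infer that the sample size, set at alpha 0.05, falls short under Fisher's test at 4.7%. The documents do not support this: the target number, event rate, chosen power and any inflation sit in Figure 2. The 906 per arm used here is an illustration, not the trial's figure. Nor can a larger loss be asserted for single anatomic sites, since no numbers per site are given and the Clinical relevance section says the trial is powered for each location.

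**Conclusion.** The concern holds in two parts of different weight. The contradiction over the primary test, and the matching one for the continuous outcomes, is certain from the text. It can decide the result only in a narrow band around 4.7%, about 1.7% of trials in the assumed 20% against 15% case. Choosing Fisher's test for the whole sample costs roughly 2 points of power across assumed control rates of 10% to 40%.

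That neither named test uses the randomisation strata is also clear, but its cost is not known. It is nil with equal risks, about 1 point with moderate differences and 3 to 5 points with wide ones, on assumed rates with four equal strata and a constant risk ratio. It would be too strong to say flatly that ignoring the strata costs power, because the documents give no complication rates by subspecialty. Both departures are conservative and add no false positives.

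**What to change.** Name one primary test, in the same words, in the abstract and in Data analysis: a Cochran-Mantel-Haenszel test stratified by subspecialty. Report it with the Mantel-Haenszel risk ratio and a confidence interval at the final level, which at 4.7% is a 95.3% interval. Restrict Fisher's exact test to sparse tables. For length of stay, pain and satisfaction, state one method in both places, with treatment and subspecialty as its factors, and so name the second factor of the ANOVA. The cost is a change of wording: no extra patients, and no data beyond the subspecialty already used to randomise.
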